### Concealment mechanism {16b}

Allocation concealment will be ensured via a central web-based system (Ennov Clinical® 7.5.720). The procedure to which a patient will be allocated will be disclosed only after enrolment in the study. Moreover, since a blocked randomization is used, the block size is not disclosed in the protocol making it impossible to predict the randomization sequence.

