## Methods: participants, interventions, and outcomes

### Study setting {9}

The study is conducted in eight transplantation centers located in University hospitals scattered throughout France. The list of participating centers is presented in Supplementary Material 1.

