### Sample size {14}

A sample size of 119 patients per randomized group (238 in total) is needed based on the following parameters:Expected decrease of EAD rate from 30% in the control group to 15% in the HOPE group (50% decrease of EAD based on previous preliminary clinical studies) [15, 20]Alpha: 0.05Power: 0.80Two-sided test

The sample size was calculated using the “pwr.2p.test” function of R (R Foundation for Statistical Computing, Vienna, Austria), package “Pwr”. In order to take into account a 10% proportion of dropouts or patients who prematurely terminate the study, 133 patients shall be recruited per group, i.e., 266 patients in total. Because there is about 20% of dropouts on the waiting list in France (2017 annual report of the “Agence de la Biomédecine”), and about 50% of liver grafts are provided from ECD, it is expected that 660 patients should be included in the study to be able to randomize 266 patients. In order not to slow down randomizations as they approach the total needed, inclusions will be possible beyond 660 patients within the limit of 1000 patients included.

According to EUROTRANSPLANT and the “Agence de la Biomédecine”, 50% of liver grafts are provided from ECD with the rate increasing over recent years. To be on the safe side, we expect that centers may randomize half of their potential transplanted patients with ECD, namely 25% of their total number of liver transplantations a year.

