## Assignment of interventions: allocation

### Sequence generation {16a}

Randomization will be performed after the allocation of the graft or after the harvesting team has macroscopically assessed the graft, according to the center practice.

It will be stratified by center and MELD score at the time of transplantation, with a cut-off of 30 (MELD < 30 versus MELD ≥ 30).

The randomization process will be centralized and carried out via Ennov Clinical software. The randomization list will be drawn up by the methodologist/biostatistician of the Clinical Research Center at the Croix-Rousse University hospital, Lyon, France.

The randomization list will be kept for 25 years in a tamper-proof envelope with the mandatory information (signature of the person in charge of the list, date and version number, complete title, and code of the research protocol). This list will also be sent to the Clinical Research Center data manager for implementation in the Ennov Clinical software.

The investigator or a person designated by the principal investigator will randomize patients via the Ennov Clinical software. Only authorized persons will be able to perform the randomization. A confirmation email will be sent to the person who performed the randomization after each randomization, to the investigator associated with the patient, and to the management center.

In case of cancellation of the transplant for any reasons, the data manager will cancel the randomization. The patient will remain included in the study for randomization in one of the study arms.

The whole process (randomization, modifications, etc.) will be recorded in the audit trail of the study, which will be integrated in the clinical data management system (CDMS). This audit trail will be transmitted at the end of the study to be archived with all the study documents.

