## Assignment of interventions: blinding

### Who will be blinded {17a}

Owing to the nature of the surgical procedure, it is not possible to blind the surgical and the anesthesiologist team for the group allocation. Because the patient cannot impact on the study outcomes after liver transplantation, there is no need to blind the patient. HOPExt is thus an open-label trial. However, in the event of isolated ALT or AST missing data for the primary endpoint, these data will be replaced by imputation on a case-by-case basis. The imputation will be performed blindly by the methodologist together with the principal investigator and will be validated by the DSMB. See the Methods in analysis to handle protocol non-adherence and any statistical methods to handle missing data {20c}. Moreover, for the analysis of the primary endpoint and some of the secondary endpoints, the data analyst will be masked to which group received the intervention (HOPE machine). A fixed code to denote each study group assignment (e.g., Group A; Group B) will be used instead.

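### Leaving the block size out of the protocol does not make the allocation sequence impossible to predict in an open-label trial blocked within center and MELD stratum

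*Protocol article*

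**What the plan says.** The section on the concealment mechanism names two safeguards. The first is a central web system that discloses the arm only after enrolment. The second, given for the blocked randomization, is the one at issue: "the block size is not disclosed in the protocol making it impossible to predict the randomization sequence". No section says whether block sizes vary.

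Other sections describe the setting:

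- **Sequence generation:** "It will be stratified by center and MELD score at the time of transplantation, with a cut-off of 30". The investigator or a delegate runs the randomization, and "A confirmation email will be sent to the person who performed the randomization after each randomization, to the investigator associated with the patient".
- **Study setting:** "The study is conducted in eight transplantation centers".
- **Who will be blinded:** "it is not possible to blind the surgical and the anesthesiologist team for the group allocation", and "HOPExt is thus an open-label trial".
- **Informed consent and the inclusion visit:** patients consent before or while on the waiting list. Randomization comes once an ECD graft has been accepted, and national allocation rules are untouched.

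**The concern.** Central web allocation hides the next assignment from direct view. It does not hide the earlier ones. In this trial each center sees every allocation in its own two strata, in order. Permuted blocks return to balance at the end of each block, so the running count of the two arms carries information about the next assignment. An investigator who tracks it does better than chance even without being told the block size, and may recover a constant size from the points of balance. Keeping the size out of a document slows this down but does not make prediction impossible.

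At stake is selection bias. A team that expects a given arm could leave an eligible, consented recipient unrandomized because of the graft or the recipient. The arms could then differ in EAD risk at baseline, and the analysis could not show that this had not happened.

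**Working it through.** **Inputs.** From the protocol article: 8 centers, 2 MELD strata, 1:1 ratio, 266 randomized, control EAD rate 30%. Block size B is not given, so B = 4, 6 and 8 are shown as an assumed range for a constant size.

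**Plan's own figures.** The article gives no figure for predictability. Its sample size reproduces: the arcsine formula for 30% versus 15% gives 118.55, rounded up to 119 per group; 119/0.90 = 132.2, rounded up to 133; 2 × 133 = 266. That is 266/8 = 33.25 patients per center and 266/16 = 16.6 per stratum.

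**Share determined in advance.** Once one arm has used its B/2 places, the rest of the block is fixed. The expected share is 1/(B/2 + 1).

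- B = 4: 1/3 = 33%, or 89 of 266. Direct count: AABB and BBAA each fix 2 places, the other four orders fix 1 each, so 8 of 24 places.
- B = 6: 1/4 = 25%, or 67 of 266.
- B = 8: 1/5 = 20%, or 53 of 266.

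Incomplete last blocks in 16 strata reduce this to about 31% (B = 4) and 22% (B = 6).

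**Correct guesses.** An observer who knows B always guesses the arm that is behind in the current block and tosses a coin at ties. The success rate is [B/2 + (2^B/C(B, B/2) − 1)/2]/B.

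- B = 4: (2 + (16/6 − 1)/2)/4 = 2.833/4 = 71%.
- B = 6: (3 + (64/20 − 1)/2)/6 = 4.1/6 = 68%.
- B = 8: (4 + (256/70 − 1)/2)/8 = 5.329/8 = 67%.

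**If the size is not disclosed.** A simulation used 33 or 34 patients per center and assumed that 10% to 30% had MELD of 30 or more. The observer knew only that B was constant and one of 2, 4, 6 or 8, and used the smallest size consistent with the center's history. This observer ended on the right size in about 96–97% of centers (B = 4) or 93–95% (B = 6), and guessed about 70% or 67% of assignments correctly. Non-disclosure therefore cost the observer almost nothing. Cancelled randomizations were not simulated.

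**If sizes vary.** With a random mix of 4 and 6, the same observer guessed about 65% correctly; with a mix of 2, 4 and 6, about 67%. The main gain is that certainty is lost. Take the first block of a stratum, with sizes 4 and 6 equally likely, after two HOPE assignments. The probability of that start is 2/4 × 1/3 = 1/6 under size 4 and 3/6 × 2/5 = 1/5 under size 6, so size 6 has posterior probability (1/5)/(1/6 + 1/5) = 6/11. The next arm is HOPE with probability 6/11 × 1/4 = 14%. Under a known block of 4 it would be 0%.

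**Illustration of consequence, under assumed behavior.** Suppose there is no true effect and every center steers EAD risk by ±5 points according to its guess. Acting only on determined assignments with B = 6 gives an apparent HOPE benefit of 2 × 5 × 0.22 = 2.2 points. Acting on every guess with B = 4 gives 2 × 5 × (2 × 0.70 − 1) = 4.0 points. In simulation, the two-sided 5% test then rejected in about 7% to 10% of null trials. The ±5 has no source in the documents.

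**The case against.** The strongest objection is that a constant size is assumed. The article speaks of the block size in the singular, but it withholds the scheme on purpose, and the full protocol may vary the sizes. This stands. It limits the magnitude and makes the fix conditional. It does not rescue the sentence, which credits non-disclosure with a property it does not have.

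The second objection is that the route to bias is narrow. Consent precedes the graft offer, consecutive candidates are screened, national allocation is unchanged, and randomization follows graft acceptance. A team therefore cannot pair a graft with a desired arm or hold it until that arm comes up. This also stands in large part. What remains is leaving an eligible, consented recipient unrandomized. Tracking two strata per center, with some randomizations cancelled, blurs the picture further.

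Two stronger readings are tempting, and neither is supported. A reader might take the sample size section, where "we expect that centers may randomize half of their potential transplanted patients with ECD", as evidence that centers choose whom to randomize. It is a cautious recruitment forecast; non-consent and the exclusion criteria could also lower the yield. A reader might also infer that the EAD comparison is biased or its type I error inflated. Nothing in the article shows steering, and the figures for it above follow from an assumed input.

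**Conclusion.** The claim that the sequence cannot be predicted is wrong for the design described, whatever the block size. How wrong depends on the undisclosed scheme. With a constant block of 4 to 8, between one third and one fifth of assignments are determined in advance and about 67% to 71% can be guessed by someone who knows or has inferred the size. With randomly varying sizes, far fewer assignments are certain, although guessing still beats chance. This is a point that should be corrected: the statement fails on the article's own text, while the practical harm is possible, limited by the timing of consent and randomization, and not demonstrated.

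**What to change.** 1. **If the block size is constant:** generate the remaining unused list with randomly varying block sizes within each center and MELD stratum. Leave out blocks of 2, whose second place is always determined. Withhold the sizes from all site investigators, including any on the steering committee. Only the statistician who draws up the list and the data manager who implements it should know them. Wording that kept them from the whole steering committee would not fit, because a methodologist and the data manager sit on it.
2. **If sizes already vary:** say so, without giving the sizes.
3. **In either case:** replace the impossibility claim. For example: *Permuted blocks of randomly varying size are used within each stratum; the sizes are not known to site investigators. This reduces, but does not remove, the chance of predicting an assignment.* If the scheme changes during the trial, state the date and the number randomized under each scheme.

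**Cost.** One list upload in the existing software, one changed sentence and, if the change counts as substantial, the amendment procedure that the article describes. Possible imbalance within a stratum rises slightly: an unfinished block can leave the arms up to B/2 apart, so 2, 3 or 4 patients for sizes 4, 6 or 8, in strata averaging about 17. Sample size and endpoint are unchanged. The benefit reaches only assignments not yet made. The trial status section says enrolment is ongoing but expects conclusion at the end of February 2023. If that date includes the 12-month follow-up, few assignments may remain. The wording correction is worth making regardless.

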### Implementation {16c}

The allocation sequence will be generated by the biostatistician. Investigators at each study site will be responsible for patient enrolment in the study. Assignment of participants to each study group will be ensured by the central web-based system (Ennov Clinical® 7.5.720®) operated by local investigators, after verification of patient eligibility and inclusion in the study.

## Assignment of interventions: blinding

### Who will be blinded {17a}

Owing to the nature of the surgical procedure, it is not possible to blind the surgical and the anesthesiologist team for the group allocation. Because the patient cannot impact on the study outcomes after liver transplantation, there is no need to blind the patient. HOPExt is thus an open-label trial. However, in the event of isolated ALT or AST missing data for the primary endpoint, these data will be replaced by imputation on a case-by-case basis. The imputation will be performed blindly by the methodologist together with the principal investigator and will be validated by the DSMB. See the Methods in analysis to handle protocol non-adherence and any statistical methods to handle missing data {20c}. Moreover, for the analysis of the primary endpoint and some of the secondary endpoints, the data analyst will be masked to which group received the intervention (HOPE machine). A fixed code to denote each study group assignment (e.g., Group A; Group B) will be used instead.

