## Trial design {8}

The HOPExt trial is a comparative open-label, multicenter, national, prospective, randomized, controlled, superiority study (1:1 ratio), in two parallel groups, with static cold storage as control.

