## Data collection and management

### Plans for assessment and collection of outcomes {18a}

Investigators are responsible for the assessment and collection of outcomes, baseline, and other trial data. Data will be entered in the electronic case report form by delegated team members and will be monitored by trained clinical research assistants (CRA) designated by the sponsor. The digitalized version of the case report form is provided in Supplemental Material 2 (French version). CRA mandated by the sponsor will ensure the proper conduct of the study, collection of written data, their documentation, recording, and reporting in conformity with the Good Clinical Practices.

The investigator and the members of their team will accept to make themselves available during the quality control visits performed at regular intervals by the CRA. During these visits, the following elements may be reviewed:Informed consentRespect of the study protocol and the procedures defined thereinQuality of the data recorded in the case report form: accuracy, missing data, consistency of the data with the source documentsManagement of the experimental treatments/strategiesDeclaration of serious adverse events

All visits will be the subject of a written monitoring report addressed to the investigator of the site visited and to the study coordinating structure.

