### Plans for collection, laboratory evaluation, and storage of biological specimens for genetic or molecular analysis in this trial/future use {33}

A metabolic assessment of the liver biopsies will be performed. Using pre-defined criteria (lactate > 8.4 and/or phosphocholine > 0.646), the level of MELG (metabolically extended liver grafts) both before and after machine perfusion will be compared within the experimental group. The level of MELG in both groups (experimental and control) will also be correlated with the risk of graft dysfunction or graft loss at 1 year.

In the control group, a biopsy of the liver graft will be taken at the beginning of the back-table preparation. Another biopsy will be taken after liver graft reperfusion in the recipient (routine practice).

In the experimental group, a biopsy of the liver graft will be taken at the beginning of the back-table preparation. Another biopsy will be taken at the end of the HOPE perfusion, and a third biopsy will be taken after liver graft reperfusion in the recipient (routine practice).

Immediately after collection (maximum 5 min after collection), the biopsy will be placed in 2-ml microvials to be either frozen in liquid nitrogen or put in allprotect®. They will then be stored at − 80 °C in each center.

Biopsies, realized at the beginning of the black-table for both groups and at the end of the HOPE perfusion for the experimental group, will be centralized at the end of the study at I-Cube laboratory (UMR 7357—Pr [name] at l) in Strasbourg, France, for analysis. Approximately 30 metabolites of interest will be analyzed by spectrometry (Brucker Avance III 500 spectrometer). A histological study of the samples analyzed by spectroscopy will also be performed. The samples will be destroyed at the end of the analysis.

Since those biopsies will be performed on a liver graft from a deceased donor, an authorization from the Agence de la Biomédecine (ABM) was required and has been obtained.

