##### Per protocol (PP)

This population includes all subjects evaluable in FAS who ended the study without any major protocol deviation, analyzed in the group to which they are allocated by randomization. Major deviations will be defined individually during a data review/blind review meeting. Major deviations detected will be, for example:Non-respect of protocol timeframe for planned visitsRandomization errors

This population will be used for efficacy analyses.

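### No outcome reader is masked: the reason given for open-label conduct does not cover whoever reads the post-reperfusion histology or the 12-month MRI/MRCP

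*Protocol article*

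**What the plan says.** The design section describes a "comparative open-label, multicenter, national, prospective, randomized, controlled, superiority study (1:1 ratio), in two parallel groups". Section {17a} gives two reasons for not blinding: "it is not possible to blind the surgical and the anesthesiologist team for the group allocation", and the patient cannot influence the outcomes after transplantation.

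The article provides masking at three points:

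- **Analysis ({17a}), for the primary and some secondary endpoints:** "the data analyst will be masked to which group received the intervention (HOPE machine").
- **Isolated missing AST or ALT values ({17a}, repeated in {20c}):** "The imputation will be performed blindly by the methodologist together with the principal investigator and will be validated by the DSMB".
- **Per-protocol definition:** "Major deviations will be defined individually during a data review/blind review meeting".

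Section {18a} assigns the assessments themselves: "Investigators are responsible for the assessment and collection of outcomes, baseline, and other trial data".

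The secondary endpoints in {12} include the post-reperfusion biopsy, read for histological change and necrosis. They also include biliary complications in the first year, assessed by three-monthly cholestasis tests and a contrast-enhanced MRI with MRCP at 12 months. According to Table 1 and its notes, both arms have the post-reperfusion biopsy and the MRI. No section says who reads them or whether that reader knows the allocation.

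**The concern.** The conclusion in {17a} is wider than its premises. That a surgeon cannot be blinded to a perfusion machine does not mean that a pathologist or radiologist must know whether it was used. Both readings involve judgement, and both feed comparisons between arms.

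The masking that is provided acts too late to help. An analyst working with groups labelled A and B receives the readings as they were made. If lesions were called more readily in known controls, the coded data already contain that difference.

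At stake is how far the histology comparison, and the imaging part of the biliary comparison, can be believed. The sample size, the type I error rate and the power for the primary endpoint are not affected.

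**Working it through.** **Who is masked, and when**

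| Step | Masked? | Timing |
|---|---|---|
| Reading of post-reperfusion biopsy | not stated | outcome is created here |
| Reading of 12-month MRI/MRCP | not stated | outcome is created here |
| Outcome assessment by investigators ({18a}) | no provision | outcome is created here |
| Imputation of isolated AST/ALT | yes | after recording |
| Deviation review | yes | after recording |
| Data analysis (primary, some secondary) | yes | after recording |

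Every masked step falls after the outcome exists.

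**The plan's own figure.** Section {14} states 119 per group for 30% versus 15%, two-sided alpha 0.05 and power 0.80. With the arcsine effect size, h = 2·asin(√0.30) − 2·asin(√0.15) = 0.3639, and n = 2·((1.960 + 0.842)/0.3639)² = 118.55, rounded up to 119. Allowing 10% dropout, 119/0.9 = 132.2, rounded up to 133. Both figures reproduce, and masking readers changes neither.

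**Illustration of a reading shift.** Inputs:

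- n = 119 per arm, borrowed from {14}.
- True lesion rate p of 15% or 20% in both arms: an assumption.
- Control readings inflated by δ: an assumption, both in size and in direction.
- Pooled z-test, two-sided 0.05, counting only significant results that favour HOPE.

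With pH = p, pC = p + δ and p̄ their mean, the chance is approximately

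Φ((δ − 1.96·SE0)/SE1), where SE0 = √(2·p̄(1 − p̄)/n) and SE1 = √((pC(1 − pC) + pH(1 − pH))/n).

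For p = 0.15 and δ = 0.05: p̄ = 0.175, SE0 = 0.0493, SE1 = 0.0492. The argument is (0.05 − 0.0966)/0.0492 = −0.947, and Φ = 17.2%.

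Summing the exact binomial probabilities over all outcomes gives:

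| Shift δ | p = 15% | p = 20% |
|---|---|---|
| 0 | 2.5% | 2.5% |
| 1 point | 4.1% | 3.9% |
| 2 points | 6.3% | 5.7% |
| 3 points | 9.2% | 8.2% |
| 5 points | 17.4% | 15.0% |

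With 100 readings per arm, the 5-point shift gives 15.4% and 13.3%. Fewer readings than 119 are plausible, because retransplanted patients are exempt from the MRI and some patients will have died.

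The model treats the biliary endpoint as a single reader's call, although {12} also uses laboratory markers. No comparable figure was computed for histology.

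**The case against.** Several objections have force.

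- **Masking is not confined to the analyst.** A reader of {17a} might infer that it is. The imputation and the deviation review are blind as well. This stands, but neither step masks anyone who produces a histology or imaging result.
- **Central tissue.** A reader might infer that the central laboratory can tell the arms apart, since HOPE patients supply two biopsies and controls one, and section {33} says "A histological study of the samples analyzed by spectroscopy will also be performed". But the central samples are the back-table biopsy from both arms and the end-of-perfusion biopsy from HOPE. The post-reperfusion biopsy is not on that list. The back-table sample precedes perfusion, and the before/after comparison is made within the HOPE group. The central tissue therefore gives no post-treatment contrast between arms for the sample count to bias.
- **Other measures inform the same objectives.** Serial transaminases and metabolic profiling also address reperfusion injury. Cholestasis tests and 1-year graft and patient survival also address late outcome. This stands. The two readings are not the only support for those claims, and the cholestasis tests offer a partial objective check on the imaging.
- **Facts not in the documents.** The article does not name the readers. That they sit outside the transplant team, and that masking them is cheap, are reasonable judgements and not documented facts. The full protocol is not shown and may specify masked reading. Even so, {17a} is the section that lists who is blinded, and it lists no reader.
- **Timing.** Enrolment began in September 2019 and conclusion was expected at the end of February 2023. Readings already made with the arm known cannot be masked by new wording.

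**Conclusion.** The point holds in a limited form. Section {17a} masks no outcome assessor, and its stated reason for open-label conduct does not extend to the readers of the post-reperfusion histology or the 12-month MRI/MRCP. The change is worth making but is not critical to the trial.

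The exposure is confined to secondary endpoints that depend partly on judgement. A reader might infer that the primary result is at risk. The documents do not support that: early allograft dysfunction is defined by bilirubin, INR and transaminase thresholds, and primary non-function by graft loss or death.

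Nor do the documents show that any reading was biased. The rise from 2.5% to about 4-17% describes sensitivity. It rests on assumed lesion rates of 15-20%, an assumed shift of 1 to 5 points against controls, and 119 readings per arm.

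**What to change.** Add to {17a} that the existing readers of the post-reperfusion biopsies and of the 12-month MRI/MRCP read without the allocation, with no arm shown on request forms or slides. Add that the reading is entered in the eCRF before any discussion with the transplant team. Apply this to all readings still to be made.

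The cost is wording on forms and labels. It needs no additional reader or patient procedure and leaves sample size, alpha and clinical care unchanged. The remaining weakness is that a local reader may occasionally learn the arm from the chart.

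A separate random code for each centralized sample is optional, since that tissue gives no post-treatment comparison between arms.
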